### Participants

Inclusion criteria will be patients’ age ≥ 18 years with ADHF confirmed within the last 24 h. Acute decompensated HF is defined as worsening in dyspnoea at rest or with minimal activity, one or more accompanying signs (jugular venous pulsation ≥ 11 cm, hepatomegaly, peripheral oedema), and one or more objective measures of heart failure (six minute walking test < 200 m, N-terminal proBNP level ≥ 1000 pg/mL or a two-fold increase to baseline).^17^ Additionally, one of the following findings has to apply: chest X-ray (presence of pulmonary venous congestion or small pleural effusion) or vena cava imaging (one of two max. diameter > 2.2 cm and/or collapsibility < 50%) or lung ultrasound (more than three B-lines in more than two intercostal spaces bilaterally are considered diagnostic for the detection of interstitial and alveolar oedema). Exclusion criteria are defined as active malignant disease, pregnancy, active severe systemic infection (requiring intravenous antibiotic treatment), end-stage renal disease with dialysis, medical or mental conditions impairing the ability to continuously wear the wearable (e.g. dementia, skin abnormalities), and active implants, which might impair recordings (detailed inclusion and exclusion criteria are listed in *Table 1*).

**Table 1 ztaf004-T1:** Inclusion and exclusion criteria for the CONAN study

Inclusion criteria	Exclusion criteria
Clinically confirmed congestion within the last 24 h NYHA ≥ II Age ≥ 18 years and able to understand the design and objectives of the study Signed written informed consent and data safety agreement before any study-related activities Willingness to wear the wearable during the treatment period and return it on a follow-up visit	Active malignant disease Pregnancy Active severe systemic infection, defined as intravenous administration of antibiotics End-stage renal disease with dialysis Medical or mental conditions, such as dementia, that hinder the continuous use of the monitoring platform and associated equipment during the monitoring period Any condition that makes wearing the wearable device impossible (e.g. presence of a shunt, active bleeding, or absence of limbs) Mental incapacity or language barriers that preclude adequate understanding or cooperation, known or suspected not to comply with study directives or not to be reliable or trustworthy, or a subject who in the opinion of the investigator should not participate in the study

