### Study procedures

In- and outpatients with ADHF will consecutively be screened for in- and exclusion criteria at the cardiology department at University Hospital RWTH Aachen (*Figure 1*). All patients will be treated according to the standard of care, and the study visits will be scheduled accordingly. The monitoring period starts from the inclusion of the patients into the study followed by continuous monitoring of vital signs and physical activity by the wearable for 90 days. Based on the decision by the treating physician eligible patients will be admitted for treatment to the study site or will be treated as outpatients. Follow-up visits are conducted on the day of discharge and in accordance with the guideline-based follow-up recommendations for patients experiencing ADHF, routine outpatient visits at the HF clinic will be scheduled ∼14 and 90 days post-discharge. If the patient initially receives inpatient treatment, the day of discharge and any unplanned visit to the outpatient clinic of the study site will be documented as study visits.

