### Data collection

Wearable data and ePRO data will be transmitted by monti via mobile data services to a centralized server that runs real-time data analysis and analysis software. The data recorded by the wearable will include time-series data of raw signals as well as vital signs and physical activity parameters, with the latter computed using proprietary algorithms provided by the manufacturer. Vital signs and physical activity parameters, such as heart rate, temperature, respiratory rate, and physical activity, will be recorded at a rate of up to 1 Hz. Thus, up to 3600 data points are potentially generated per hour, each paired by a corresponding quality index. On the platform backend, data integrity is assessed by monitoring actual wearing time, both initial and ongoing app usage, and overall data quality. Data integrity assessments are conducted at interim study visits and the study’s conclusion (*Table 2*).

Clinical records (visit entries, laboratory results, diagnostic results) will be documented in worksheets. Records will be independently and retrospectively reviewed by two cardiologists for the presence of ADHF. Worksheet entries and results of the validated questionnaires are transferred into a database.

Time-series data recorded by the wearable will be annotated based on clinical records. At each follow-up visit, where a clinical congestion assessment is conducted, the 2 days prior and post-visit are annotated as either ADHF or regular, as determined by the congestion assessment on the visit day.

Exploratively, the dataset of regular episodes may be enriched by including episodes beyond this initial 2-day window if patients report stable symptoms and vital signs through the app. This approach allows for the evaluation of whether these additional episodes show consistent ‘regular’ patterns suitable for model training. Datasets will be split into hours according to their timestamps, and only hours with a >90% amount of data points will be included to ensure sufficient information content among hours. No predefined quality constraints are used.

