To calculate the risk index, ‘regular’ hours collected during the study are used to train a deep neural network with a self-supervised contrastive learning objective, extracting features typical of regular periods. Training and test data are split 90/10. The model is used to calculate a risk index that measures the dissimilarity to regular features. The detection and predictive performance of the risk index will be compared to clinical documentation of ADHF. To evaluate the risk index’s predictive capabilities over time, the timestamp of the clinical ADHF diagnosis will be used as a reference point. The risk index computed by the model will subsequently be examined for the days preceding an ADHF event. This analysis aims to identify early deviations in the risk index that could potentially be driven by subclinical changes in physical activity or vital sign patterns.

Data collection will be conducted following an intention-to-treat approach and will continue until withdrawal, except in cases where there is a specific request to delete all individually recorded data.

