### Statistical analysis

The sample size calculation was based on a 20% incidence rate of congestion, an 85% detection sensitivity of the risk index (see below), a 15% dropout rate, a 10% error tolerance, and a significance level of 0.05, indicating a need for ∼282 patients to achieve sufficient statistical power.

For statistical analysis differences between means of hours annotated as ‘regular’ and ‘congested’ obtained from risk score will be tested for significance using a two-sided *t*-test test, adjustment for multiple comparisons is performed by using Bonferroni correction. To address overfitting, a 10-fold cross-validation will be performed. Statistical significance will be tested by an analysis of variance within the cross-validation splits of ADHF and regular. Receiver operating characteristics analysis [area under the curve of the ROC-analysis (AUROC)] will be computed to assess the primary endpoint. The cut-point that optimizes the detection of true positive results (sensitivity) and false positive results (1-specificity) is reported by the Youden index. For clinical requirements (not missing an event), specificity will additionally be reported at a sensitivity of ∼95%.

To assess risk score prediction capabilities for congestion detection, the performance of the score up to 7 days before and after the timestamp of diagnosis (t = 0 h) will be analysed. For AUROC-analysis, 95% confidence intervals are reported. A *P*-value of <0.05 will be considered significant. For data and statistical analysis, an open-source software tool will be used.

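### The 7-day look-back before an ADHF diagnosis does not separate a new decompensation from the index episode in which every patient enters the study

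*Protocol article*

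**What the plan says.** All references are to the protocol article.

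- **Entry state (Participants):** "Inclusion criteria will be patients’ age ≥ 18 years with ADHF confirmed within the last 24 h".
- **Start of recording (Study procedures):** "The monitoring period starts from the inclusion of the patients into the study followed by continuous monitoring". Each record therefore opens inside the index episode.
- **Visits (Study procedures):** for patients first treated as inpatients, "the day of discharge and any unplanned visit to the outpatient clinic of the study site will be documented as study visits". Table 2 also lists any unplanned visit, such as an emergency attendance, as a study visit.
- **Labels (Data collection):** at each follow-up visit, "the 2 days prior and post-visit are annotated as either ADHF or regular, as determined by the congestion assessment on the visit day". Records are "independently and retrospectively reviewed by two cardiologists for the presence of ADHF". The question put to the reviewers is presence, not new onset.
- **Time zero (Data collection):** "the timestamp of the clinical ADHF diagnosis will be used as a reference point".
- **Reading of the earlier days (Data collection):** "This analysis aims to identify early deviations in the risk index that could potentially be driven by subclinical changes" in activity or vital-sign patterns.
- **Window (Statistical analysis):** "the performance of the score up to 7 days before and after the timestamp of diagnosis (t = 0 h) will be analysed", introduced as a test of the score's ability to predict.

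No section requires a regular visit, a symptom-free interval or any other sign of recovery between the index ADHF and a later ADHF label.

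**The concern.** A look-back is evidence of early warning only if the patient was out of the event state when the window opened. This cohort starts in the event state and is recorded from that moment. If a patient is still decompensated at the next assessment, that visit supplies a time zero. The days before it are then overt index ADHF, not the subclinical run-up that Data collection sets out to find. A raised index on those days shows only that the episode has not ended.

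The Conclusion presents the study as an evaluation of pre-emptive detection, and this analysis is the one that bears on it. The Discussion itself treats a change in congestion state within the two-day annotation window as unlikely, so the authors already assume short-term persistence.

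**Working it through.** **1. The plan's own figure, which sets the event count.** Inputs from Statistical analysis: 20% incidence, 85% sensitivity, 10% error tolerance, 15% dropout, significance level 0.05.

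- 1.96² × 0.85 × 0.15 / 0.10² = 48.98
- 48.98 / 0.20 = 244.9
- 244.9 × 1.15 = 281.6, which reproduces the stated figure of about 282
- Evaluable follow-up events, assuming one per affected patient: 282 × 0.85 × 0.20 ≈ 48 (≈ 49 with the abstract's 290)

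**2. Where the look-back falls.** Take inclusion as day 0 and an ADHF label on day T. The look-back covers day T − 7 to T, cut at the start of recording. The baseline diagnosis has no look-back, because recording starts after it. Only follow-up labels matter.

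| Case | Recorded look-back | Inside the index episode? |
|---|---|---|
| Inpatient rated ADHF at discharge, stay of 7 days or less | day 0 to T | wholly inside the index admission |
| Treated as an outpatient, returns on day 4 still decompensated | day 0 to 4 | wholly |
| Never decongested, any T of 7 or more | all 7 days | wholly |
| Relapse 5 days after a discharge rated regular | days −7 to −5 are the 2 days before discharge | no; the plan annotates them as regular |

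Table 2 places Visit 1 at day 14 ± 7. At its earliest, day 7, the look-back begins on day 0. Study procedures counts this visit from discharge instead. That reduces the overlap for inpatients at Visit 1, but not at the discharge visit or for patients treated as outpatients.

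**3. How many events could be exposed (assumed onset times).** If the index state lasts k days, the look-back reaches into it when T ≤ 7 + k.

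- Onset uniform over 90 days: share = (7 + k)/90. For k = 2, 7 and 14 this is 10.0%, 15.6% and 23.3%, or 4.8, 7.5 and 11.2 of 48 events.
- Early-clustered onset (exponential with mean m, truncated at 90 days): share = (1 − e^(−(7+k)/m)) / (1 − e^(−90/m)). For m from 45 down to 20 this is 21–37% (k = 2), 31–51% (k = 7) and 43–66% (k = 14).

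These are timing shares only. They overcount patients who had a regular assessment in between, and they miss patients who stay congested for longer.

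**4. Effect on an apparent day −7 AUROC (assumed values).** With fixed controls, the AUROC is an average over cases. A mixture with carry-over share f therefore gives (1 − f) × A₀ + f × A₁. Assume no true warning (A₀ = 0.50) and carry-over cases that separate like established ADHF (A₁ = 0.85).

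- f = 0.100: 0.900 × 0.50 + 0.100 × 0.85 = 0.535
- f = 0.156: 0.844 × 0.50 + 0.156 × 0.85 = 0.555
- f = 0.233: 0.767 × 0.50 + 0.233 × 0.85 = 0.582

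The sign depends only on A₁ > A₀. The amount depends on f and A₁, and the document fixes neither.

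**The case against.** **A condensed article may leave an episode rule to a fuller document, and a maximum of 7 days leaves room to truncate.** This is fair for a missing detail. But the article does fix the label rule, the time zero, the window and the interpretation, and together these do not separate new from persisting ADHF.

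**The ADHF definition under Participants requires worsening breathlessness, and two cardiologists review the records.** This could screen out some persistent cases, such as residual congestion at discharge without worsening. It is stated as the entry definition, however. The follow-up rule in Data collection rests on the visit-day assessment and does not repeat it.

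**Early relapse after discharge is not in itself a problem.** A reader might infer that any relapse within a week of discharge is contaminated. The document does not support that. If discharge is rated regular, the two days before it are annotated regular and belong to the data from which regular features are learned. The look-back passes beyond them only for a relapse within 5 days: 5/90 = 5.6%, or about 2.7 of 48 events under uniform onset. The mixture then gives 0.50 + 0.056 × 0.35 = 0.52.

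**The effect may be lost in noise.** With 49 cases and an assumed 200 controls, the standard error of a null AUROC is about 0.046, a 95% half-width of about 0.09. The illustrated shifts lie inside that. This limits how visible the bias would be, but it does not remove a systematic upward error.

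**Lead time is not an endpoint.** Correct: Table 4 lists no pre-diagnosis outcome, and the wording in Data collection is hedged.

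**Conclusion.** The concern holds for ADHF labels at a discharge or early unplanned visit with no regular assessment since the index episode. There, the plan as written counts persistence as early warning. The bias is upward provided the risk index is higher in persisting congestion than in true pre-onset days.

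Its size cannot be derived from the document. The range 0.535 to 0.582 rests on assumed onset times, an assumed index duration, an assumed carry-over AUROC of 0.85 and no true warning. It shows scale and is not an estimate.

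A reader might also infer that the primary AUROC is inflated. That does not follow: the primary objective is to detect diagnosed ADHF, and a persisting episode is still a true case for that purpose. The point is confined to the pre-diagnosis analysis. It deserves correction because the claim of pre-emptive detection leans on that analysis.

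**What to change.** In Data collection (risk index) and Statistical analysis, add one analysis rule:

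1. Base the main look-back analysis on ADHF diagnoses preceded by at least one assessment annotated regular after the index ADHF.
2. Start each look-back no earlier than the beginning of that regular-annotated window, that is, 2 days before the regular visit.
3. Report all other follow-up ADHF labels separately as *index episode not documented as resolved*, and give the look-back results with and without them.

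The group in step 3 should not be called persistent. Patients treated as outpatients have no discharge visit, so some will have recovered and relapsed before their first scheduled assessment.

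The rule uses labels already collected. Its cost is fewer events in the lead-time analysis, with some early relapses moved to the separate group. As a rough guide, removing the uniform-onset shares above would leave about 43, 40 or 37 of 48 events. The 95% half-width for a sensitivity of 85%, 1.96 × √(0.1275/n), would go from 10.1 to 10.7, 11.0 or 11.5 percentage points. The primary AUROC needs no change.

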All study equipment will be collected at the end-of-study visit. In the event that no data is received from an enrolled patient for 1 day, the patient is reminded via a push notification to use the monitoring system. If no data is received for 2 consecutive days, the patient is contacted by phone to determine whether there is a technical problem. If the patient wishes to terminate the study, he will be excluded and asked to return the devices at the next regular visit to the study site. If this is not possible, the study team can offer to collect the devices at the patient’s home. If a patient is lost to follow-up, he will be contacted during the next regular visit to the study site to return the equipment.

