### Outcome and objectives

The primary outcome of this pilot study with the monti platform will be the accuracy of detecting episodes with diagnosed ADHF by a self-supervised contrastive learning-derived risk index based on wearable-recorded time series assessed through *C*-statistics (*Table 4*). As a secondary outcome data integrity will be assessed through the percentage of wearable data per day, the time difference between logged time point of measurement and database, and the score in the SUS, will be evaluated. Additionally, several exploratory endpoints will be examined.

**Table 4 ztaf004-T4:** Objectives and outcome measures of the CONAN study

	Outcome measures
Primary objective	
Assess the capability of the self-supervised contrastive learning-derived risk index (from wearable-recorded time series) to detect episodes of acute decompensated heart failure (ADHF).	Area under the receiver operating characteristics (AUROC) curve for detecting episodes of diagnosed ADHF.
Secondary objective	
(2) Evaluate the data integrity of the *monti*-monitoring platform in terms of adherence, technical functionality, and data quality.	Adherence: Daily percentage of wearable data availability. Percentage of data availability over participation period. Availability of each parameter per day. Number of app-server connection attempts. Number of uploaded vital signs. Number of recorded ECGs. Number of dropouts. Technical functionality: Ratio of failed uploads to total uploads. Number/type of notifications sent via the app. Number/type of user contacts. Mean time difference between measurement and database logging. Data quality: Mean percentage of data with high quality indices determined by the wearable for each parameter per day.
(3) To assess usability of the mobile *monti* platform	Mean score on the System Usability Scale (SUS). Percentage of users rating the app as ‘easy to use.’
(4) Monitor adverse events, including device-related effects and deficiencies.	Number of skin reactions or discomfort. Number of observed device damages.
Explorative objective	
(5) Expansion of the dataset by including additional ‘regular’ episodes	Number of ‘regular’ episodes included for training, annotated based on the 2-day window of study visits. Number of the additional ‘regular’ episodes included for training, annotated based on patient-reported stable symptoms and vital signs via the app. AUROC detecting episodes with diagnosed ADHF with expanded training data.

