### Limitations

A limitation of the study is that the reliability of this risk index relies on the robust pattern recognition of regular episodes by high quantity and quality of the training data. Challenges include the continuum of clinical congestion from subclinical congestion without symptoms to full symptomatic presentation. Clinical congestion is not a binary condition and clinicians may incorrectly rate congestion. Therefore, different approaches to diagnose and grade clinical congestion are assessed.

By using the provided smartphone for data transfer, patients will likely leave the smartphone at home, which leads to a delayed transfer of the study data, when the wearable has no connection for data transfer. However, a provided smartphone is mandatory due to challenges such as data privacy and security concerns.

To evaluate the clinical benefit of a remote monitoring solution, a randomized controlled study has to be considered as the gold standard that provides stronger evidence. Such a study design will be the next step in determining the outcome benefits of such an approach for patient care. However, the study protocol presented in this manuscript has been conceptualized as a functionality and usability study before further research on comparing outcome benefits.

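### The analysis of the 7 days before diagnosis times the signal; without regard to upload time it does not support a conclusion on pre-emptive detection by the platform

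*Protocol article*

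**What the plan says.** All references are to the protocol article.

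- **Reference point.** Under Data collection, "the timestamp of the clinical ADHF diagnosis will be used as a reference point", and the index is then examined over the preceding days to look for early deviations. Under Statistical analysis, "the performance of the score up to 7 days before and after the timestamp of diagnosis (t = 0 h) will be analysed".
- **Clock of the wearable data.** Under Data collection, "Datasets will be split into hours according to their timestamps". The text does not say whether this means measurement time or database time.
- **Expected delay.** Under Limitations, "patients will likely leave the smartphone at home, which leads to a delayed transfer of the study data".
- **Follow-up of gaps.** Under Wearable-based monitoring platform, one day without data leads to a push notification. "If no data is received for 2 consecutive days, the patient is contacted by phone".
- **Use made of the delay.** Table 4 (Outcome and objectives) lists it as a technical measure under the data-integrity objective: "Mean time difference between measurement and database logging". It is not linked to the 7-day analysis.
- **Claim.** The Conclusion says the study will evaluate the efficacy and safety of the platform in detecting congestion pre-emptively, and will cover the whole chain from recording to delivery of the index.

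**The concern.** A platform can warn only on data it has received. If the index is placed at the time of measurement, an hour recorded before the diagnosis but uploaded afterwards adds to the apparent performance before diagnosis, although no index could have been computed from it at that time. The article foresees late uploads, records the delay, and still draws a conclusion on pre-emptive detection by the platform. Nothing in the text restricts the pre-diagnosis analysis to data then on the server.

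At stake is how the results for the 7 days before diagnosis are read. As a description of when vital signs and activity begin to change, they are sound on this point. As evidence of how early the platform could have raised an alarm, they can only err on the favourable side. A mean delay over all data would not show whether late uploads happened to fall shortly before ADHF presentations.

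**Working it through.** **Is measurement time the clock?** It is inferred, on two grounds. Hours are kept only if more than 90% of their data points are present, which makes sense on the recording clock. The secondary outcome also treats the logged measurement time and the database time as two separate quantities. The article does not state the clock outright.

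**Is there a planned figure to reproduce?** No. The article states neither a lead time nor a delay, and the sample size does not enter this point.

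**Inputs.** Window before diagnosis: 7 × 24 = 168 h (Statistical analysis). Gap thresholds: 24 h for the reminder and 48 h for the phone call (Wearable-based monitoring platform). The delay D is not given, so constant values are assumed. The thresholds serve as reference values and are not upper bounds.

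**Formulas.**
- Share of the window not on the server at diagnosis = D / 168.
- Share of the last 48 h not on the server at diagnosis = D / 48, for D up to 48 h.
- Usable warning time = time of the signal before diagnosis − D.

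| Assumed D | Share of 168 h missing at diagnosis | Share of last 48 h missing | Usable warning from a signal 24 h before diagnosis |
|---|---|---|---|
| 1 h | 1/168 = 0.6% | 2.1% | 24 − 1 = 23 h |
| 12 h | 12/168 = 7.1% | 25% | 24 − 12 = 12 h |
| 24 h | 24/168 = 14.3% | 50% | 24 − 24 = 0 h |
| 48 h | 48/168 = 28.6% | 100% | 24 − 48 = −24 h (after diagnosis) |

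**A milder assumed pattern.** Suppose the patient is away from the phone for 8 h each day and the data upload on return. Then 8/24 = 33% of hours arrive late, by 4 h on average, which is 0.33 × 4 = 1.33 h over all hours. Earlier absences have already uploaded by the time of diagnosis, so at most 8/168 = 4.8% of the window is missing then.

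The effect therefore runs from negligible to material, and the documents do not say where in this range the study will lie.

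**The case against.** The case on the other side is substantial, and much of it stands.

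- **Measurement time suits the stated aim.** Data collection describes a search for early deviations that subclinical changes might cause. That is a question about physiology, and arrival time would not answer it. This stands, and the measurement-time analysis should stay.
- **No lead time is promised.** Table 4 has no such outcome. This stands. A reader might infer that the plan overstates its lead time, but it defines none. The overstatement arises only if the results before diagnosis are read as platform warning, which is the reading the Conclusion invites.
- **The delay is measured and disclosed.** True, but only its mean is listed, it is not tied to the pre-diagnosis analysis, and the Conclusion is not qualified by it.
- **The analysis is offline anyway.** Records are reviewed retrospectively and the network is trained on hours collected across the study. Restricting to received data would not by itself turn this into real-time performance. This stands: the restriction is necessary for a platform claim but not sufficient.
- **This is detail for an analysis plan.** The absence of an extra sensitivity analysis from an article would be no finding. The point is the mismatch within the article between its analysis, its own limitation and its conclusion.

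Two stronger readings are tempting. The first is that a share of episodes would be credited as detected with nothing on the server, costing many points of sensitivity. A 48 h gap leaves 168 − 48 = 120 h of the window unaffected, and the documents give no frequency for such gaps, so no loss of sensitivity can be derived. The second is that acutely ill patients have the longest gaps. The documents do not support this either: the stated mechanism is a phone left at home, and a housebound patient would be near it.

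**Conclusion.** The point holds in a limited form. On the natural reading, the analysis of the 7 days before diagnosis runs on measurement time. That is correct for signal timing, but it does not support the Conclusion's statement on pre-emptive detection by the platform, because hours uploaded after diagnosis would count as pre-diagnosis performance.

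The direction is certain: delay can only reduce what was available for a warning. The size is not known. It depends on a delay distribution that the documents do not give, and the 0.6% to 28.6% range rests on assumed constant delays of 1 to 48 h. The primary AUROC on annotated hours does not depend on arrival time and is unaffected. This is a worthwhile, inexpensive correction to a supporting analysis of a pilot study.

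**What to change.** 1. State that the main analysis of the 7 days before diagnosis uses measurement time and describes when the signal changes.
2. Repeat it using, at each time point, only hours whose database timestamp is at or before that time. Report how many episodes have no received data at that point.
3. Base any platform-level statement on pre-emptive detection on this second analysis. Otherwise, limit the Conclusion to retrospective signal timing.

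Both times are already needed for the secondary outcome on transfer delay, so no new data, patients or procedures are required. The cost is a little extra analysis and possibly a less favourable early-detection result. The primary analysis and the signal-timing analysis stay as they are.
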